## Abstract

**Introduction:**

Chronic migraine is a largely refractory condition affecting between 1 and 2.2% of the overall population worldwide, with females more affected than males. There are also high health and socioeconomic costs associated both for the individual and society. The mainstay of chronic migraine management is pharmacological, but the options available have limited efficacy and there are often unwanted side effects. There is some evidence for manual therapy as a treatment option for migraine, but its effectiveness for chronic migraine is unknown. Therefore, we have designed a pragmatic randomised control trial to investigate whether adding manual therapy to the tertiary specialist treatment of chronic migraine improves patient-reported outcomes.

**Methods:**

A pragmatic, randomised controlled trial in a hospital tertiary headache clinic**.** Participants will be randomised into one of two groups: treatment as usual or treatment as usual plus manual therapy. The primary outcome measure will be a change in the Headache Impact Test score. Secondary outcomes will also be measured over the 12-week study period including changes in headache frequency, migraine specific quality of life and reductions in relevant medicine consumption. The manual therapy group will have five treatment sessions each lasting 30 min. The recruitment target of 64 participants will allow power at 80% with *p* = 0.05 using minimal clinical difference for Headache Impact Test of 3.7 and includes provision for a 10% dropout rate. Recruitment will take place between August 2018 and February 2019. The results will form part of a doctoral study and be published in peer-reviewed journals and presented at national/international conferences.

**Discussion:**

Current pharmacological approaches have limited effects in the management of chronic migraine and there is a requirement to improve treatment options and reduce the health and economic burden of the condition. Manual therapy has been shown to be effective in other chronic pain conditions as well as other primary headaches. This study will explore the effectiveness of manual therapy as an adjunctive approach to the management of chronic migraine.

**Trial registration:**

The trial has received a favourable opinion from the UK Health Research Authority (IRAS 228901) and is registered at ClinicalTrials.gov.number NCT03395457. Registered 1st March 2018.

## Background

Migraine is experienced by the vast majority of sufferers as episodic migraine (EM) [1, 2] occurring regularly although not necessarily frequently, with around 65% of sufferers estimated to have a migraine episode fortnightly to monthly [3]. However if the episodic pattern becomes uncontrolled, a process of chronification occurs whereby the original episodic migraine becomes very frequent and more disabling. This is termed chronic migraine (CM) and is described by the International Headache Society (IHS) classifications [4] as “*headache occurring on 15 or more days per month for more than three months, which, on at least 8 days per month, has the features of migraine headache*”. On the days without migraine headache the individual can often suffer from pre and post headache effects adding to the burden of this condition.

The management of CM is more complex than EM, as it is often resistant to standard treatments with resultant additional costs compared to EM. The mean (SD) annual cost per CM person ($8243 [$10,646]) was over three times that of those with EM ($2649 [$4634]). Both direct medical costs and cost of lost productivity were substantially higher in CM than EM [5]. In addition to financial costs, the social costs and personal impact of CM often leads to severe disability for those with CM [6, 7]. This is especially true for females, with the annual prevalence of CM in women being 1.7–4.0% compared to men (0.6–0.7%) [8–11]. Those women aged between 18 and 49 years of age are the most affected across the range of measures. In one study, CM sufferers were found to be three times more likely to have lost work and have reduced household productivity than those with EM (58% compared to 18%) [12]. People with CM are also much more likely to report “very severe headache-related disability” as measured by the Migraine Disability Assessment Scale (MIDAS) than those with episodic (24.8 and 3.2% respectively) [13, 14].

Despite the suggestion that migraine is a syndrome with multiple pathological mechanisms which support a multi therapeutic approach rather than a single approach [15–17], the mainstay of treatment for CM is pharmacological. However, some patients do not want, or cannot, take some prophylactic medications such as Topiramate due to restrictions in its use [18]. Currently, OnabotulinumtoxinA (Botox) is the only specifically licensed treatment for CM in the UK [19]. Although its mechanism of action is unclear, studies have demonstrated that injecting specific sites on the head and neck produce significantly beneficial effects in CM patients. One study concluded that 32% of CM patients achieved a 50% reduction in headache days and a 50% reduction in migraine days, with NICE guidance recommending a 30% reduction in headache days as a measure of success in Botox studies [20]. Although similar clinically significant reductions in the Headache Impact Test (HIT 6) scores are seen with Botox and Topiramate interventions, Botox has fewer side effects and higher adherence rates [21, 22]. However, the efficacy of Botox in those patients who benefit only partially or not at all from Botox, and its relatively high cost, are barriers to an increased uptake [23–25]. Therefore if adjunctive therapies, especially those with fewer side effects and relatively low costs could be utilised, this may increase the benefit to more of those with CM.

One possible adjunctive intervention is manual therapy. Despite the mechanisms of its potential action in CM being unknown, the basis for its potential role can be garnered from studies in associated conditions. These include primary headaches (tension type and migraine), as well as common comorbidities; chronic pain and specifically neck pain. One systematic review concluded that MT has an efficacy in the treatment of chronic tension headache equal to that of prophylactic medication with tricyclic antidepressant [26]. Another involving massage therapy and chiropractic spinal manipulative therapy concluded that they may be as efficient as Propranolol and Topiramate in migraine prophylaxis. It also concluded that there is moderate quality evidence for both spinal manipulation and mobilisation as suitable treatments in chronic non-specific neck pain [27]. These studies found benefits in at least one of the following: frequency, duration and intensity of headaches/pain.

Currently there are two theories in existence relevant to this study of manual therapy in the management of chronic migraine. One is that migraine is, in part, an abnormal response in those genetically pre-disposed, to nociceptive input involving the nerves of the upper cervical spine (C1, C2 and C3) and associated joints and muscles. This leads to exaggerated sensitisation of the trigeminal pathway and subsequent face, neck and head pain [28–30].

The other theory incorporates the allostatic model in which people respond to stressful events, actual or perceived, with physiological and behavioural changes. In general these changes maintain normal physiological stability (allostasis). However, if stressors (including ongoing pain or nociceptive inputs) become too great or frequent then the normal response can become dysfunctional as a result of allostatic loading, which itself alters brain structure and function. Likewise, repeated migraines are themselves thought to be a driver of changes to the brain structure that may lead to a dysfunctional allostatic response. Consequently, many migraine sufferers report that stressful activities of daily living (physical and emotional) exacerbate their migraines [31, 32].

Chronification from EM to CM may be a result of the stress mechanisms generating the migraine or as a consequence of changes in the brain arising in response to the attacks. Therefore if stressors (for example nociceptive pain, and central sensitisation, possibly from musculoskeletal disorders) can be reduced, this may add to the efficacy of existing interventions [33].

Whilst the process of chronification in CM is not fully understood, there are a number of known associated risk factors including head and neck injury, and other pain disorders [34] (Table 1).

**Table 1 Tab1:** Risk factors associated with migraine chronification and reversion

• Obesity	
• Snoring	
• Sleep disorders	
• Excessive caffeine intake	
• Psychiatric/psychological disease (Depression/Anxiety)	
• High baseline headache frequency	
• Overuse of migraine abortive drugs	
• Major life changes	
• Head or neck injury	
• Cutaneous allodynia	
• Female sex	
• Comorbid pain disorders	
• Lower socioeconomic status	

(Adapted from Schwedt, 2014, [79])

Currently, one of the most common factors in chronification is considered to be the presence of medication over use headaches (MoH) due to the frequent use of opioids and barbituates in self medication of headaches, or in association with concomitant conditions. Estimates of between 30 and 72% of CM patients presenting at tertiary clinics are thought to have MoH associated chronification [35, 36]. The IHS diagnosis of medication overuse is made if abortive drugs are used regularly for more than three months on 10 or more, or 15 or more, days a month, depending on the drug. One study estimated a twofold increase in chronification with opioid use on 8 days a month [37]. Therefore any studies of interventions in CM should include a detoxification phase or a process to mitigate CM with MoH being included.

Both of the above migraine models suggest a role for altered sensory processing in the brainstem, which is associated with the presence of central sensitisation and one of the consequences, cutaneous allodynia (CA). Some studies cite CA as more prevalent in CM than EM, whilst others suggest there is little difference and it is more a reflection of migraine duration. There are a few potential reasons for these differences which include: the type of CA – thermal, dynamic and static mechanical; how it is measured and the temporal nature of CA making it difficult to measure consistently; and its role as a marker for the risk of frequent attacks rather than simply a consequence of frequent attacks [38, 39]. CA is also consistently reported more in females than males (49.7% vs 32.6%%, *P* < 0.001) [40] and is common in other chronic pain conditions, with its presence associated with a reduction in the efficacy of abortive treatments [41, 42].

Various models of MT and pain reduction exist which involve biomechanical, neurophysiological and psychological components, either individually or in combination. However all of these models consider that MT may work by activating descending inhibitory pathways via different levels of the spinal cord [43–45]. The common relationship of central sensitisation, the cervical spine, and pain disorders (see Table 1) would suggest MT may have utility in the management of CM.

In terms of potential as an adjunctive treatment, MT has been shown to reduce pain and have a direct effect on the mechanics of the cervical spine that results in functional improvements [46–48]. MT has also been shown to increase local pain pressure thresholds, which are used to detect central sensitisation [49, 50]. Consequently, MT may reduce cutaneous allodynia and improve the efficacy of current approaches to treating CM.

The above discussion outlines commonalities between migraine, other pain conditions, its chronification and the potential for MT in its treatment. Combined with evidence showing the scope for improvement in existing CM treatment, this suggests there may be potential for the use of adjunctive non-pharmacological treatments, especially if these are generally associated with lesser side effects [16, 51].

The objective of this study is to determine the effectiveness of MT as an adjunctive therapy to tertiary care (‘care as usual)’ in CM.

## Methods

### Study design

This will be a single centre, pragmatic Randomised Controlled Trial (RCT) involving 64 participants. The two groups will be “Tertiary care as usual” and “Tertiary care as usual plus MT”. The objective of the study is to measure the difference between the two treatment groups in CM. The study design adheres to the IHS and Consolidated Standards of Reporting Trials (CONSORT) guidelines [52, 53]. The study flow is outlined in Fig. 1.

**Fig. 1 Fig1:**
[figure not shown]
Participant flow

### Participants

#### Recruitment

Participants will be recruited between August 2018 and February 2019 through the Salford Royal NHS Foundation Trust acute neurology clinic service in the UK. The neurologist and specialist headache nurse will identify potential participants from their list of existing CM patients.

Details of this study will be sent to potential participants with their clinic appointment letter. Eligible participants will be female aged greater than 18 years of age, and diagnosed with CM according to the criteria of the International Classification of Headache Disorders (ICHD-III) by their neurologist. The enrolment in to tertiary care requires that patients must be free of medication over use headache and as part of the inclusion criteria (Table 2), participants will have gone through a detoxification phase and had at least one cycle of tertiary care treatment to further mitigate medication overuse headache. Exclusion criteria for this study are: contraindication to MT including spinal radiculopathy; uncontrolled psychological conditions; and any physical or MT in the last 6 weeks. Acute and abortive migraine medication will continue as usual during the study.

**Table 2 Tab2:** Inclusion and exclusion criteria

Inclusion Criteria	
• Females over 18 years of age	
• A good command of English (to enable informed consent)	
• Existing patients with chronic migraine as diagnosed by a clinical interview with a neurologist in line with the International Classification of Headache Diagnosis criteria (ICHD)	
• Undergoing care as usual from the neurologist	
• Must have had at least one cycle of treatment from neurologist and not be a new patient	
Exclusion Criteria	
• Currently having or had manual therapy to the neck or shoulder in the previous six weeks.	
• A new patient without any existing management by neurologist	
• Having a condition contraindicated for manual therapy including, but not limited to, inflammatory disorders, severe osteoporosis and tumours.	
• Identification of any medical ‘red flags’ by the neurologist.	
• Evidence of any central nervous system involvement for example:	
o Facial palsy (presence of ptosis/Horner’s syndrome)	
o Visual disturbance (presence of blurred vision, diplopia, hemianopia)	
o Speech disturbance (presence of dysarthria, dysphonia, dysphasia such as expressive or receptive)	
o Balance disturbance (presence of dizziness, imbalance, unsteadiness, falls)	
o Paraesthesia (presence, location such as upper limb/lower limb, face)	
o Weakness (presence, location such as upper limb/lower limb)	
o Known major psychiatric or psychological conditions not under control	

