#### Allocation

A randomisation assignment sequence will be created by an independent member of the research team using randomisation software “Research Randomizer” [60]. The results will be put into sealed opaque envelopes which the participants will open in their meeting with the PI, who will explain the process to be followed depending on the group allocation.

Immediately following the initial screening by the neurologist/specialist nurse, those participants who meet the inclusion criteria will be invited to an assessment with the Principal Investigator (PI). If this is not possible, it will be arranged within 5 days. The PI will provide participants with verbal and written information about the project before gaining written consent. He will also explain the risks, and benefits as well as the potential adverse reactions to MT and how to manage them. Potential adverse reactions may include temporary local tenderness, aching and tiredness [61]. Participants will be randomised into two groups (care as usual and care as usual plus MT).

The neurologist will be blinded as to the participant’s group allocation in order to reduce initial selection and potential contact bias. The PI cannot be blind to the manual therapy group but will be blinded to the end of study survey analysis, with an independent member of the research team detailed to recode the participant reference numbers and store the key file on a password protected computer. The unblinding of single cases by the PI/CI in the course of a clinical trial will only be performed if necessary for the safety of the trial subject.

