#### Scientific value

CM is a highly disabling condition with few evidence-based treatment options. In the UK, Botox is the only specifically approved pharmacological intervention, although Topiramate and occipital nerve injections are used in tertiary clinics. This study will aim to explore the outcomes of MT as an adjunct to those receiving ‘care as usual’ for CM in a tertiary setting. It will also provide information relating to central sensitisation in the form of CA for participants, which will contribute to a body of knowledge in those with CM and support tailoring treatment options.

Although this will be a pragmatic study, the results of this study will only be applicable to the target group - females over 18 years of age with CM under tertiary care. The approach used will however be generalisable to all manual therapists with the requisite training in techniques used. Undertaking the study in a specialist medical headache clinic should help to build the nascent relationship between medical headache specialists and manual therapists. Post study dissemination will potentially help the development of more multidisciplinary approaches.

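### Women whose chronic migraine is already controlled can enter, and no headache-day count before allocation is listed to identify them or to anchor the >50% reduction outcome

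*Protocol article*

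**What the plan says.** Under Recruitment, "The neurologist and specialist headache nurse will identify potential participants from their list of existing CM patients". Table 2 requires "Existing patients with chronic migraine as diagnosed by a clinical interview with a neurologist in line with the International Classification of Headache Diagnosis criteria (ICHD" criteria, care as usual from the neurologist, and that the woman "Must have had at least one cycle of treatment from neurologist and not be a new patient". The diagnosis carries no date. The criteria set no minimum for current headache days, migraine days or HIT-6 score, and no re-confirmation after the treatment cycle. The reason given for the prior cycle is to reduce medication overuse headache. Allocation describes the step before consent and randomisation: "Immediately following the initial screening by the neurologist/specialist nurse, those participants who meet the inclusion criteria will be invited to an assessment".

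The Background defines CM as "headache occurring on 15 or more days per month for more than three months", with migraine features on at least 8 of those days. It also reports, from one Botox study, that "32% of CM patients achieved a 50% reduction in headache days and a 50% reduction in migraine days".

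Under Data collection, the baseline set is demographic information, HIT-6, MSQ, PSS-10, STAI-6, Brief Cope, HADS, ASC-12, BMI and pressure algometry. Headache days come from weekly diaries kept during the 12 weeks. Table 5 includes the percentage of women whose monthly headache days fall by more than 50%.

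**The concern.** New patients are excluded, so every entrant has had at least one treatment cycle that may have moved her below the article's own CM threshold. Nothing printed in the criteria then stops her entering.

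Three things follow. First, a woman already controlled may have less to gain on HIT-6. If there are enough such women, the average between-group difference shrinks, and a null result could partly reflect who was enrolled. Second, without a headache-day count taken before allocation, nobody can tell afterwards how many such women there were or examine the effect without them. Third, the responder outcome needs a starting value and none is stated. The early diary weeks are a poor substitute, because manual therapy sessions are planned for Weeks 1 and 2.

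Scientific value applies the results to "females over 18 years of age with CM under tertiary care". That description is loose if some women no longer meet the definition.

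**Working it through.** **Can a controlled woman qualify?** A 50% reduction from a starting frequency D leaves D/2 days. D/2 is 15 or more only if D is 30 or more: 20 becomes 10, 28 becomes 14, 30 becomes 15. Almost any woman who halves her headache days therefore drops below the Background definition, while still satisfying Table 2 as printed.

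**The plan's own figure.** Inputs from Sample size: difference 3.7, SD 4.91, alpha 0.05, power 80%, equal groups. Sidedness is not stated; two-sided reproduces the result.
- Standardised effect: 3.7/4.91 = 0.754.
- Two-sample t-test: 28.6, so 29 per group, as stated. Power at 29 per group is 80.5%.

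The sample size has no arithmetic error, and at 29 analysed per group there is almost no margin.

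**Illustrative dilution.** Let f be the share of entrants already controlled, and E the true effect in the others. If controlled women gain nothing, the mean effect is E(1 − f). If they gain half, it is E(1 − f/2). SD is held at 4.91 with 29 analysed per group. The documents do not give f. The value 32% is borrowed from the Botox response rate as an upper illustration only.

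With E = 3.7:

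| f | Effect, no gain | Power | n per group for 80% | Effect, half gain | Power |
|---|---|---|---|---|---|
| 0 | 3.70 | 80.5% | 29 | 3.70 | 80.5% |
| 10% | 3.33 | 72% | 36 | 3.52 | 76% |
| 20% | 2.96 | 62% | 45 | 3.33 | 72% |
| 32% | 2.52 | 48% | 61 | 3.11 | 66% |

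With E = 8.74, the HIT-6 difference that the Discussion cites for osteopathy plus medication against medication alone, and no gain in controlled women:
- f = 32%: 8.74 × 0.68 = 5.94, power above 99%.
- f = 50%: 8.74 × 0.50 = 4.37, power 91%.

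The loss thus depends on f, on the benefit in controlled women and on E. The documents fix none of these.

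**The responder outcome.** A woman treated down from 20 to 10 days before entry must fall below 5 to count if the reference is her current frequency. If the reference is her original 20, she needs only to fall below 10, and is almost there at entry. The article does not say which applies, and no listed baseline item supplies either number.

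**The case against.** A reader might infer that controlled women do enter and do pull the effect below 3.7. The documents do not support that. Table 2 speaks of existing patients with chronic migraine and a neurologist or specialist nurse screens each one, which can be read as requiring CM now. Fig. 1 and Table 4 are not shown, so a baseline step displayed there cannot be excluded. The 32% is a response rate from one Botox study, not the share of this clinic's list below 15 days, and usual care here also includes other treatments. The abstract calls 3.7 the minimal clinical difference, not the expected effect in uncontrolled women. All of this stands, and it turns the power figures into a sensitivity range.

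A reader might also infer that breadth contradicts the rationale, because the Background refers to "those patients who benefit only partially or not at all from Botox". That is background about Botox. The stated objective is manual therapy as an adjunct to tertiary care, without restriction to non-responders. In a pragmatic trial a mix of treatment responses may be intended. Requiring 15 or more current days would even exclude some partial responders, for example a woman who has gone from 20 to 13 days. A compulsory threshold is therefore not the obvious remedy.

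Baseline HIT-6 is collected, so women with low impact can be found on the primary scale. That answers part of the concern, but HIT-6 does not show whether a woman still meets a frequency definition. The responder problem applies to both arms alike, so it affects sensitivity and interpretation and does not by itself create bias.

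**Conclusion.** The point holds as a gap in what is recorded and in how the population is described. As printed, women below the article's own CM threshold can enter, and no listed pre-allocation measure identifies them by frequency. They may dilute the HIT-6 difference. On the least favourable illustration (no benefit in 10% to 32% of entrants, true effect exactly 3.7 in the rest, SD 4.91, 29 per group) power is 72% to 48%; on the 8.74 figure there is little loss. Neither illustration can be preferred from the documents, and no actual power loss is demonstrated. The missing reference for the >50% outcome does not depend on any of these assumptions. The weight is moderate: a cheap improvement worth making, with the sample size calculation left as it stands.

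**What to change.** Keep the pragmatic entry criteria and make these changes:

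1. At the existing screening interview, before allocation, the neurologist or nurse records headache days and migraine days for the last month.
2. Use the headache-day count together with baseline HIT-6 as covariates in the between-group HIT-6 analysis.
3. Name the same count as the reference for the >50% reduction outcome.
4. Prespecify, as supportive only, the HIT-6 contrast in women with 15 or more current headache days.
5. In Methodological considerations and Scientific value, describe the population as women with a CM diagnosis under tertiary treatment.

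The cost is one recalled count per woman and a few lines of analysis wording, with no effect on recruitment. A one-month recall is less precise than a diary and cannot confirm a definition that runs over more than three months, so it serves as a descriptor and covariate, not as proof of diagnosis. If any women fall below 15 days, the supportive contrast rests on a smaller sample than the main test. With fewer than 29 per group its power for 3.7 points is below 80.5%, and a null result there should carry little weight.
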